#### Specific objectives

❖ To determine the differential between the ages and gender of the children in respect of knowledge, awareness, practice and child drowning.❖ To develop and assess the initial response of a community to an intervention package in terms of acceptability, feasibility and sustainability.❖ To determine the social-demographic factors (educational level of parents, occupation of parents, social-economic status of parents and medical condition), environmental factors (places of residence, time of day, time of season, distance from the house, place of drowning, safety equipment, presence of lifeguard, activity immediately before drowning and mothers activity) and behavioural factors (supervision practices of parents and swimming ability of parents and child) through pre-test and post-test on knowledge, awareness, practice and child drowning.❖ To understand the perception of the community concerning the problem of drowning and its possible implications for designing a preventive programme for the rural areas of Bangladesh.❖ To identify the association between the knowledge, awareness and practice of child drowning with social-demographic variables, environmental variables and behavioural factors.❖ To evaluate the mobile coach for its effectiveness.❖ To determine the risk factors based on social-demographic, environmental and behavioural factors in respect of childhood drowning, knowledge, awareness and practice pertaining to child drowning.

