### Randomisation and allocation concealment

To avoid spillover effects within the villages, we will conduct a cluster randomised controlled trial using the village as the randomisation unit. Due to the heterogeneity of participants in various disciplines (e.g. gender or educational level), we will use separate randomisation lists for each village (stratified randomisation). Furthermore, for approximate equality of sample size in the study groups, we will use computer generated block randomisation. The study assistants supervising the baseline assessment in the villages will be blinded concerning the group allocation of the village. In addition, group allocation will not be released to the study participants until they provide informed consent, their username, mobile phone number and baseline data. Furthermore, the study assistants conducting the face-to-face interviews at follow up will be blinded when assessing the primary and secondary outcome measures.

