### Sample size calculation

The following formulae for hypothesis testing of the two group comparison was used [16] *N* = {Z1 – α/2 √2P̃ (1 – P̃) + Z1 – β √P1 (1 – P1) + P2 (1 – P2)}^2^ / (P1 – P2)^2^. P1 = Proportion of drowning in boy children aged under five years 55 % = 0.55; and P2 = Proportion of drowning in girl children aged under five years 45 % = 0.45 [17]. P̃ = (P1 + P2)/2 = 0.5 and adjusting for 10 % non-response *N* = 392+ 10 % of 392 = 431. A sample size of *N* = 431 in each study group would have 80 % power for a Chi-Square Test (*α* = 5 %, 2 *sided*) in order to detect this difference based on a calculation using G-Power. As union participants are nested within villages, a potential design effect needs to be considered. An assumed number of participants per village of 30 and an intra-cluster correlation coefficient of 0.05 could be expected. This would result in a design effect = 1+ (m-1) × ICC = 1+ (20–1) × 0.05 = 1.95. Multiplying this design effect by the “required size for an unnested sample (*N* = 431)” results in a required sample size of *N* = 840 per study group and a total of *N* = 1680 study participants.

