### Data analyses

The data will be entered into SPSS statistical package version 22.0.

The proportion, mean and standard deviation will be used to quantify the level of knowledge, awareness and practice before and after intervention.

The paired *t*-test will be used to examine the effectiveness of the intervention programme by comparing the pre-test and post-test score in respect of knowledge, awareness and practice.

The chi-square test will be worked out to determine the association of the socio-demographic, environmental and behavioural factors with childhood drowning.

In addition, the risk factors for childhood drowning with socio-demographic, environmental and behavioural factors will be determined using multivariate logistic analysis.

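### The chi-square and logistic risk-factor analyses, as named, ignore the villages, so standard errors are too small for factors that cluster by village

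*Protocol article*

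**What the plan says.** Under Randomisation and allocation concealment the protocol article states: "we will conduct a cluster randomised controlled trial using the village as the randomisation unit". Sample size calculation carries this forward: "As union participants are nested within villages, a potential design effect needs to be considered". It then gives the inputs, "An assumed number of participants per village of 30 and an intra-cluster correlation coefficient of 0.05 could be expected", and computes the design effect as "1+ (20–1) × 0.05 = 1.95".

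Data analyses names two methods for the risk-factor aim. The first is "The chi-square test will be worked out to determine the association of the socio-demographic, environmental and behavioural factors with childhood drowning". The second is a model for the same groups of factors, which "will be determined using multivariate logistic analysis". Neither sentence mentions village, a random effect, generalised estimating equations (GEE) or a cluster-robust variance.

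Identifying risk factors is part of the secondary outcome, both in Design and main hypothesis and in Outcomes. The Specific objectives also extend the aim beyond drowning: "To identify the association between the knowledge, awareness and practice of child drowning with social-demographic variables", and likewise with environmental and behavioural factors.

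**The concern.** The article allows for clustering in the sample size but names analyses that do not. An ordinary chi-square test and an ordinary logistic regression both assume independent observations. Where the outcome and the factor both cluster by village, each parent adds less information than these methods assume. Standard errors come out too small, and a nominal 5% test rejects more often than 5%.

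At stake is the reliability of any claim that a factor is associated with the outcome, for an aim the article lists as a secondary outcome. The test of the intervention effect is a separate matter and does not depend on this point.

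**Working it through.** **The plan's own figure.** Inputs from Sample size calculation: proportions 0.55 and 0.45, two-sided 5%, power 80%.

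- n = {1.96 × √(2 × 0.5 × 0.5) + 0.8416 × √(0.55 × 0.45 + 0.45 × 0.55)}² / 0.10² = (1.3859 + 0.5921)² / 0.01 ≈ 391.3, so 392.
- 392 + 10% = 431.2, taken as 431.
- 431 × 1.95 = 840.5, stated as 840 per group and 1680 in total.

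The stated sample size reproduces. The clustering allowance is therefore a working part of the plan.

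**Cluster size.** The article gives several values: 20 in the design-effect formula, 30 in the sentence before it, 5 villages per group in Study settings and population (840/5 = 168 parents per village), and 15 per group in Baseline survey (840/15 = 56). All are carried through.

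**Upper bound: a factor constant within villages.** Design effect DE = 1 + (m − 1) × 0.05. The true standard error is √DE times the naive one. The true level of a nominal 5% test is 2 × {1 − Φ(1.96/√DE)}.

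| Parents per village (m) | DE | SE too small by a factor of | True level | 1680/DE |
|---|---|---|---|---|
| 20 | 1.95 | 1.40 | 16% | 862 |
| 30 | 2.45 | 1.57 | 21% | 686 |
| 56 | 3.75 | 1.94 | 31% | 448 |
| 168 | 9.35 | 3.06 | 52% | 180 |

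Simulated null data with outcome prevalence 10% or 50% agreed: about 21% at m = 30, 31% at m = 56 and 52% to 53% at m = 168.

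**Partly clustered factors.** Use DE = 1 + (m − 1) × 0.05 × ICC of the factor. The article gives no ICC for any factor, so 0.1 to 0.3 is an assumption.

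- m = 20: DE 1.095 to 1.285, true level 6% to 8%.
- m = 56: DE 1.275 to 1.825, true level 8% to 15%.
- m = 168: DE 1.835 to 3.505, true level 15% to 30%.

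**Factors varying fully within villages.** In simulation the naive test rejected in about 4% of null runs, so there is no inflation.

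**Drowning as the outcome.** The Background gives 156.4 per 100,000 for rural children aged 1–4, taken here as yearly. Follow-up is six months.

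- Expected deaths with one eligible child per household: 1680 × 0.5 × 156.4/100,000 = 1.3. With two (an assumption): 2.6.
- Six-month risk p = 0.5 × 0.001564 = 0.00078. For a between-village coefficient of variation (CV) of the risk, ICC = CV² × p/(1 − p). An assumed CV of 0.25 to 1 gives ICC 0.00005 to 0.0008.
- Over m = 30 to 168 this gives DE 1.00 to 1.13 and a calculated level of 5.0% to 6.5%.
- An ICC of 0.05 would need a CV of √(0.05 × (1 − p)/p) ≈ 8.
- In simulation (CV 0.5 and 1) the naive chi-square test rejected in only about 0.5% to 0.9% of null runs, because there are too few events.

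**The case against.** The strongest objection is that Data analyses ties both tests to drowning alone. For drowning deaths at the article's own rate, clustering adds almost nothing and sparse events are the real limit. That stands. A reader might infer from the table that village-related factors will often be declared causes of drowning by chance. The documents do not support that, since 16% to 52% needs an ICC of 0.05 in the analysed outcome and none is given for drowning as an analysed outcome. If non-fatal or earlier drownings were counted there would be more events, but the article gives no rate for them.

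Second, most of the listed factors differ between households or between events rather than between villages: parental education, supervision, swimming ability, distance from the house, time of day. This also stands, and it is why the table is an upper bound.

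Third, the article does not say that chi-square or logistic methods will be used for knowledge, awareness and practice, and a fuller plan might name something else. This stands in part. The objective is stated, knowledge has a yes/no classification in Outcomes, and no other association method is named, but carrying the two tests over to these outcomes is an inference.

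Fourth, a reader might conclude that the models pool both arms without an arm term. The article gives no covariate list and does not say whether the arms are combined, so this cannot be asserted.

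The objection does not remove the mismatch. This is more than a detail left to an analysis plan: the article names specific tests, and as named they do not fit the nesting that it describes and budgets for.

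**Conclusion.** The point holds in limited form. The two methods named for the risk-factor aim assume independence, while the article's own design and sample size say participants are clustered in villages. Standard errors will be too small for factors that cluster by village.

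For common outcomes such as the knowledge classification, if these tests are used there and the ICC is 0.05, the true level of a 5% test is bounded above by about 16%, 31% and 52% at 20, 56 and 168 parents per village. It falls towards 5% as the factor varies more within villages. For drowning deaths the inflation is negligible: with about 1 to 3 expected events the multivariable logistic model is not estimable, and the tests are uninformative rather than too liberal.

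This rests on the article's ICC applying to the analysed outcome, on its rate being yearly, and on the assumed factor ICCs and between-village variation. The correction is worth making because the aim is a stated secondary outcome and the change is cheap, but it does not bear on the test of the intervention.

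**What to change.** In Data analyses, replace the two sentences on association with a model that accounts for village: either a village random intercept, or GEE clustered on village with a small-sample correction, which matters with as few as 5 villages per group. Include study arm whenever end-line data from both arms are combined. Use a logistic model for the binary knowledge classification and a linear model for the summated knowledge, awareness and practice scores, because Outcomes gives no cut-point for the last two. Report drowning events descriptively if they are too few to model.

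Reconcile the stated village numbers and cluster sizes at the same time, since they determine how much the adjustment matters and which small-sample method is suitable.

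No new data are needed, because village is the randomisation unit and is known for every participant. The cost is wider intervals for clustered factors and slightly more analysis work.

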### Project monitoring and quality control

The Ministry of Science and Technology and Centre for Injury Prevention and Research, Bangladesh, collectively agrees with the planning, monitoring and evaluation processes employed in the project. The Ministry of Science and Technology, Bangladesh, has approved significant financial assistance.

### Outcomes

The outcomes of the study will be to determine the knowledge, awareness and behaviour practices about childhood drowning, as well as the risk factors, and reduce the incidence of childhood drowning. To determine the knowledge pertaining to childhood drowning, five questions about the knowledge of childhood drowning are provided. The questions will be answered YES or NO. A correct answer will score one mark and a zero mark will be given for an incorrect answer. The participants will be classified as having knowledge of drowning if they correctly answer all five questions. Based on those five questions, the total summated score will be calculated. Five questions will be used to measure the awareness about childhood drowning. Based on the five questions, the total summated score will be calculated. The behaviour practices will be divided into supervision practices and swimming ability. In addition, five questions will be used to measure the behaviour practices. Based on the five questions, the total score will be calculated. The study assistants will conduct the six-month follow up assessment by field interviews. The primary outcome will be the monthly assessment of increased knowledge, and safety awareness and practice about childhood drowning. The secondary outcome will be the assessment of reducing the incidence of children drowning to compare the baseline data and end line data, and also to determine the risk factors for childhood drowning. Finally, the outcome variables will be the effects of the mobile coach Intervention on the community in Bangladesh.

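### Supervision and swimming ability define the practice outcome and are also the behavioural factors that two objectives set against practice, so that association cannot be read as a determinant of practice

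*Protocol article*

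**What the plan says.** Three sections of the protocol article bear on this.

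- **Outcomes.** On practice: "The behaviour practices will be divided into supervision practices and swimming ability". The next sentence reads "In addition, five questions will be used to measure the behaviour practices", and those questions give a total score. Practice belongs to the primary outcome: "The primary outcome will be the monthly assessment of increased knowledge, and safety awareness and practice about childhood drowning".
- **Specific objectives.** The third objective lists the explanatory variables. Among them are "behavioural factors (supervision practices of parents and swimming ability of parents and child" (the bracket closes there). Two later objectives use these factors. The fifth is: "To identify the association between the knowledge, awareness and practice of child drowning with social-demographic variables, environmental variables and behavioural factors". The seventh is: "To determine the risk factors based on social-demographic, environmental and behavioural factors in respect of childhood drowning, knowledge, awareness and practice pertaining to child drowning".
- **Data analyses.** The test of association is named for one outcome only: "The chi-square test will be worked out to determine the association of the socio-demographic, environmental and behavioural factors with childhood drowning". The logistic analysis is likewise for risk factors for drowning. Practice appears in this section only in the descriptive summaries and the paired t-test.

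**The concern.** Supervision and swimming ability are on the outcome side in one section and on the explanatory side in another, and two objectives join the two sides. Read literally, those objectives ask whether supervision and swimming ability are associated with supervision and swimming ability.

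What is at stake is the reading of a secondary result. A report that follows these objectives could present supervision or swimming ability as a strong correlate of, or risk factor for, poor practice. The finding might reflect only how the score was put together, or that two sets of questions measure one thing. Programme planners could take it for a lever to improve practice.

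**Working it through.** The plan gives no figure to reproduce here. The check is a comparison of definitions, followed by an illustration of size.

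**Step 1: the definitions side by side.**

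| Role | Section | Content |
|---|---|---|
| Outcome: practice | Outcomes | supervision; swimming ability (whose ability is not stated) |
| Explanatory: behavioural factors | Specific objectives, third | supervision by parents; swimming ability of parents and of the child |
| Link: association | Specific objectives, fifth | practice against behavioural factors, among others |
| Link: risk factors | Specific objectives, seventh | behavioural factors, among others, for practice |

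The constructs coincide, and both links are explicit. No sentence exempts practice from either objective or says that the factor measures are separate from the five practice questions.

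**Step 2: what follows if questions are shared.** Assumptions, none of them from the documents: five mutually independent items of equal variance s², with k of them also serving as the factor. Let F be the sum of the k items and T the total of all five.

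- Cov(F, T) = k s², Var(F) = k s², Var(T) = 5 s²
- Correlation = k / sqrt(5k) = sqrt(k/5)
- k = 1: 0.45; k = 2: 0.63; k = 3: 0.77; k = 4: 0.89

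The items have no relationship with one another, so all of this correlation is overlap.

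**Step 3: the same on a cut score.** Further assumptions: yes/no items, prevalence 0.5, and good practice defined as 4 or more of 5. The article gives no such cut for practice.

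- P(total ≥ 4, given item = 1) = P(at least 3 of the other 4) = 5/16
- P(total ≥ 4, given item = 0) = P(all of the other 4) = 1/16
- Odds ratio = (5/11) / (1/15) = 75/11 = 6.8

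**Step 4: sensitivity to the assumed cut and prevalence.** The planned size is a "required sample size of *N* = 840 per study group and a total of *N* = 1680 study participants". A simulation used N = 840 and N = 1680, a different cut (3 or more of 5), prevalences of 0.3, 0.5 and 0.7, and 1000 runs per setting. The chi-square test at the 5% level rejected as follows.

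- One of the five items tested against the cut total: 100% of runs in every setting.
- A separate, unrelated item: 4.4% to 5.3% of runs, close to the nominal level.

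**Step 5: what follows if questions are not shared.** The algebra in steps 2 and 3 no longer applies. Two sets of questions on the same construct can be expected to correlate, but by an amount that the documents do not let one compute.

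**The case against.** The strongest reply has four parts.

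1. **No practice model is specified.** This stands. The Data analyses section names chi-square and logistic analyses for drowning alone. A reader might infer that a planned multivariable model of practice would have its variance taken up by the overlapping terms, hiding real socio-demographic or environmental determinants. The article contains no such model, so that inference is not supported. What remains is that two stated objectives call for the comparison.

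2. **Overlap of items is not shown.** This also stands. The questionnaire is not in the article. The words "In addition" that open In addition, five questions will be used to measure the behaviour practices allow a reading in which the five scored questions are separate from the supervision and swimming measures, though they may be no more than a connective. The factor also covers the child's swimming ability, which the outcome text does not mention. A reader might conclude that the association is guaranteed by construction. That is true only if the same questions feed both sides, which the document neither says nor rules out.

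3. **The sizes rest on assumed inputs.** Agreed. The cut, the prevalence, the independence of items and the number shared are all assumptions, and yes/no scoring is stated only for the knowledge questions. The figures show what sharing would do, not that sharing occurs.

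4. **An article leaves item-level detail to fuller documents.** This is fair for the questionnaire and for the predictor list of each model. It does not answer the point, because the article itself defines both sides with the same two constructs and states the objectives that join them.

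**Conclusion.** The point holds as a contradiction between the Specific objectives and the Outcomes section. The same two constructs are both outcome and explanatory factor, so an association of practice with the behavioural factors cannot be read as identifying a determinant of practice, whichever questions are used.

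Its size is conditional. With shared questions, and under the illustrative assumptions, one shared item of five already gives a correlation of 0.45, and an odds ratio of 6.8 at a cut of 4 or more, with no real relationship present. Significance at the planned sample size would then be practically certain. With separate questions the size is unknown and nothing is forced.

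The reach is limited to a secondary question. A reader might infer that the primary result is compromised because practice is part of the primary outcome. It is not: the between-arm comparison of practice does not use the behavioural factors. The analyses with drowning, knowledge or awareness as the dependent variable are also free of this overlap.

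**What to change.** Amend the fifth and seventh specific objectives in one of two ways.

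- **Exclude.** State that when practice is the dependent variable, supervision and swimming ability are not explanatory factors, and only the socio-demographic and environmental factors are used.
- **Separate.** Restrict the behavioural factors used against practice to measures that form no part of the practice construct or its score, and name them. Using different questions on supervision and swimming would remove the part-whole overlap but leave the same construct on both sides.

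In either case supervision and swimming ability can stay as factors for knowledge, awareness and drowning. A sentence in Outcomes saying which questions make up the practice score, and whose swimming ability they cover, would remove the remaining ambiguity.

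The cost is the wording of two objectives, plus a matching line in any analysis specification that covers practice. No new data, no change in sample size and no change to the trial's main comparison are needed.

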## Discussion

This study protocol is to determine the design of a cluster randomized controlled trial testing concerning the efficacy of mobile coach intervention to increase the knowledge and safety awareness, and practice about childhood drowning among the parents with children, and reduce the incidence of childhood injuries. This is the first controlled trial testing of the efficacy of mobile coach based childhood drowning intervention in a population consisting mainly of parents with children. Due to the realization of participant recruitment, it is also the first trial to test the efficacy of mobile coach based intervention in parents with children in terms of increasing their understanding pertaining to the risks of childhood drowning. Among the limitations of the study is that the majority of drowning cases go unrecorded, due to a lack of adequate survey data in hospitals and clinics, information bias and dependence on other data sources, such as police data and post-mortem data. Given that the mobile coach intervention is effective, it would provide an attractive, cost-effective model to increase the knowledge and awareness about childhood drowning and reduce childhood drowning in rural Bangladesh. The programme could be easily disseminated nationwide or via national prevention campaigns or internationally to other middle/low-income countries.
